### Outcomes

2.3

The primary outcome is to evaluate the rates of patients who received a complete protocol of pneumococcal vaccination six months after hospitalization. The coordinating pharmacist of the study will collect this outcome by calling the GP or the home care nurse. The national health data system (SNDS) of the NHI, which lists all medications delivered to patients [22], will also be checked to verify the dispensation of vaccines by community pharmacy. A protocol will be considered complete only if the two vaccines (PCV13 and PPSV23) were administrated.

One of the secondary outcomes will assess prescriptions of pneumococcal vaccination protocol and traceability of the indication of vaccination in the discharge letter. The clinical pharmacist will collect this information in the unit at discharge. Later on, the rates of incomplete vaccination protocol 6 months after the hospitalization will be evaluated. The rate of incomplete protocols will be calculated by dividing the number of patients with incomplete vaccination protocols to the total number of patients, transformed in percents. An incomplete protocol is determined by dispensation and administration of PCV13, not followed by administration of a second injection of PPSV23. As for the primary outcome, the SNDS will be checked and the healthcare staff administrating will be contacted to confirm the administration of the first vaccine but not the second one. The SNDS will also be consulted to analyze the primary dispensation of vaccines by community pharmacy 6 months after hospitalization. The matching between the SNDS data and declarations of community pharmacies about dispensations of vaccines will be also evaluated. The declarations of community pharmacies will be collected after a call by the pharmacist coordinating this study. Finally, a subgroup analysis will be done to compare the difference between clinical and surgical units and university hospitals and hospitals.

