## Background

1

*Streptococcus pneumoniae* (pneumococcus) is a cocci gram-positive bacterium which is responsible for invasive pneumococcal diseases (IPD) like meningitis and bacteremia or more common infections like otitis and community acquired pneumonia. In France, in 2020, pneumococcus was the first cause of bacteremia (5.2 cases/100,000 inhabitants) and meningitis (0.7 cases/100,000 inhabitants) [1]. It is also the main cause of bacterial pneumonia [2]. Children under 5 years old and elders are more likely to develop pneumococcal infections [1,3,4], but other populations are considered at risk, like adult patients with immunodeficiency or patients with some specific comorbidities (cardiac, renal, respiratory failure, diabetes, etc.) [5].

Pneumococcal infections are an economic burden for society. In Europe, all documented cases of pneumonia generate costs around €10 billion per year [6]. In France, the average hospitalization fee for a community acquired pneumococcal pneumonia is €7,293, the follow-up fee being €1241 [7]. Furthermore, the World Health Organization (WHO) included pneumococcus on a priority pathogens list for research and development of new antibiotics, because of the antibiotic resistance of the pathogen, especially against penicillin [8,9]. Pneumococcal pneumonia is also considered the evitable disease with the highest mortality rate [10], explaining that vaccination could be a major health issue.

In France, 2 vaccines against pneumococcus are available: 23-valent pneumococcal polysaccharidic vaccine (PPSV23) and a 13-valent pneumococcal conjugate vaccine (c) [11,12]. In 2017, the High Council for Public Health (HCPH) recommended a sequential vaccination with PCV13 followed by a shot of PPSV23 8 weeks later for all patients older than 5, considered at risk of pneumococcal infections [13,14]. For patients having received just one dose of VPP23, it is recommended to do a dose of PCV13 after 1 year.

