### Intervention

2.4

During the control period, the patient management will be as usual: the pharmacist in the unit will do a medication reconciliation and check his pneumococcal vaccination status. If the patient is eligible for vaccination based on HCPH criteria [14] but not vaccinated according to three sources [20,21], the pharmacist will note it in the patient's medical record. During the month after discharge, the pharmacist of the unit will check pneumococcal vaccines prescription and notification of vaccination indication in the discharge letter by the department physician. Six months after the end of hospitalization, the coordinating pharmacist of the study will call the patient's usual community pharmacy to check vaccine dispensation. He will also call the patient's general practitioner and/or home care nurse to check the vaccine administration. Finally, the SNDS will be analyzed to check all vaccine dispensation.

Concerning the experimental stage, the pharmacist of the unit will also do medication reconciliation, check the vaccination status of patient and report it in the medical record. If it is negative, the pharmacist will communicate the vaccination benefit to the physician the vaccination benefit. Then the physician will suggest the pneumococcal vaccination and prescribe the protocol with patient agreement. He will note vaccination indication in the discharge letter for the GP. Before the patient returning home, the pharmacist will have a pharmaceutic discharge conversation with the patient and explain the benefits of vaccination and the protocol (dispensation and administration). The pharmacist will also send a pharmaceutic discharge letter to the patient's usual community pharmacy about pneumococcal vaccination. The follow-up procedure and the data collected will be the same for the two phases. For ethical reasons, the coordinating pharmacist will inform the GP of the recommendation to vaccinate all unvaccinated patients of the study at the end of their follow-up. The OPTIVACC study's flow of intervention is outlined in Fig. 2.

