## Discussion

3

This trial will assess the impact of the collaboration between pharmacist and physician on increasing the pneumococcal vaccination of at-risk patients when they return home after hospitalization.

The IP-VAC trial [24], a single center study made by the Nimes University Hospital preliminary to OPTIVACC, showed an increase of vaccines dispensation by community pharmacy. By collecting data on vaccine administration from GPs or home nurses, OPTIVACC study wants to demonstrate an impact on pneumococcal vaccination coverage. To harmonize the data collection, phone calls will be centralized and performed by one officer. In addition, consultation of the NHI database at the end of the study should allow an exhaustive collection of all the vaccine doses administered to the patients.

In addition, consultation of the NHI database at the end of the study should allow an exhaustive collection of vaccines administered to the patients. Intervention will be evaluated in two types of care units (clinical and surgical) and two types of establishments (hospitals and university hospitals). The aim of these comparisons is to define in which context the intervention will be most relevant, in order to target eligible care units.

Patient recruitment will be a critical point of this study, even though there are many indications for pneumococcal vaccination. Firstly, it is difficult to check patients' vaccination status. According to a study carried out as part of the “INNO'vaccins programme”, one patient in two does not know whether he/she is up to date with his/her vaccinations [25]. For this reason, medication reconciliation, a process carried out by the clinical pharmacist to list all patient's medication on hospital admission, is the first step before including a patient in the study.

Although all of the participating centers carry out clinical pharmacy activities, most of them have never conducted clinical research projects. In this sense, initial training of the centers' personal and coordination of the project are two key points for the success of the study, particularly in terms of patients’ recruitment and follow-up.

Patient follow-up will run for a period of six months after discharge to allow the patient to complete the vaccination protocol, which takes at least 8 weeks.

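### The 6-month incomplete-protocol rate mixes patients whose second vaccine was due and not given with patients whose second vaccine was not yet due

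*Protocol article*

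**What the plan says.** All references are to the protocol article.

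- **Timing of the assessment** (2.3 Outcomes): "Later on, the rates of incomplete vaccination protocol 6 months after the hospitalization will be evaluated".
- **Numerator** (2.3): "An incomplete protocol is determined by dispensation and administration of PCV13, not followed by administration of a second injection of PPSV23". No minimum time since PCV13, latest start date or not-yet-due category is given.
- **Rate** (2.3): obtained by "dividing the number of patients with incomplete vaccination protocols to the total number of patients", so the denominator is everyone, not only those who started.
- **Interval between the vaccines** (1 Background): the French authority "recommended a sequential vaccination with PCV13 followed by a shot of PPSV23 8 weeks later".
- **Reason for six months** (3 Discussion): follow-up runs for "six months after discharge to allow the patient to complete the vaccination protocol, which takes at least 8 weeks".
- **Both phases** (2.4 Intervention): "The follow-up procedure and the data collected will be the same for the two phases".
- **Primary outcome** (2.3), also at six months: "A protocol will be considered complete only if the two vaccines (PCV13 and PPSV23) were administrated".

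Section 2.8 analyses the binary secondary outcomes by mixed logistic regression. Section 2.6 plans on 20% in the control group and 40% in the experimental group.

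**The concern.** The two clocks start at different events. Follow-up is counted from the end of hospitalization, but the second vaccine is timed from the first. A patient who receives PCV13 late in follow-up reaches the six-month check before 8 weeks have passed. That patient meets the definition of incomplete although nothing has been missed. The label therefore covers two situations: the second vaccine was due and not given, or it was not yet due.

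The rate is compared between phases, so the mixture matters. Its not-yet-due part depends on how many patients start and when they start, and both could differ by phase. Intervention patients are to be offered a prescription before discharge, have a pharmacist consultation and have a letter sent to their community pharmacy. Control patients receive usual care with a note in the record. A difference in the incomplete rate could then reflect starting behaviour rather than what happens after the first dose.

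**Working it through.** The plan gives no figure for this outcome to reproduce. The check is calendar arithmetic, followed by a sensitivity calculation on assumed start times.

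**1. Affected window.** Inputs: six months from discharge, taken as 182 days (2.3), and 8 weeks = 56 days (Background).
- Latest start that reaches 8 weeks by the check: 182 − 56 = day 126, or week 18.
- Share of the window after that day: 56/182 = 30.8%.

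**2. Share of starters who start late.** The documents give no start-time distribution, so these are assumptions. For exponential start times with median m weeks, F(t) = 1 − 2^(−t/m), and the late share among those who start within six months (26.1 weeks) is L = [F(26.1) − F(18.1)]/F(26.1).

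| Assumed start times | Late share L |
|---|---|
| median 2 weeks | 0.2% |
| median 4 weeks | 3.3% |
| median 8 weeks | 11.6% |
| median 13 weeks | 17.6% |
| median 26 weeks | 23.7% |
| uniform over follow-up | about 31% |

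**3. Not-yet-due labels as a share of all patients.** Assume every starter receives PPSV23 exactly 8 weeks after PCV13. Everyone labelled incomplete is then simply not yet due. With completion c at six months (20% control, 40% intervention, section 2.6):
- starters s = c/(1 − L)
- labelled incomplete = s − c

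*Control starts uniform, all intervention starts by day 126:*
- control s = 20%/0.692 = 28.9%, labelled 8.9%
- intervention labelled 0%
- the intervention looks about 9 points better

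*Both uniform:*
- control 8.9%
- intervention s = 40%/0.692 = 57.8%, labelled 17.8%
- the intervention looks about 9 points worse

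*Median start 8 weeks in both:*
- control 20%/0.884 − 20% = 2.6%
- intervention 40%/0.884 − 40% = 5.2%
- the intervention looks 2.6 points worse

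*Median 8 weeks in control, 4 weeks in intervention:*
- control 2.6%
- intervention 40%/0.967 − 40% = 1.4%
- the intervention looks about 1 point better

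Behaviour after the first dose is identical in every scenario, yet the sign changes. Because the denominator is all patients, a phase with more starters also has more late starters unless its starts are sufficiently earlier.

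**4. Composition of the label when some second doses are missed.** Assume 10% of starters are late and 20% of the earlier starters miss the second dose. The not-yet-due share of those labelled incomplete is 0.10/(0.10 + 0.90 × 0.20) = 0.10/0.28 = 36%.

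**The case against.** The best defence is that the outcome is a status at a fixed time: one vaccine but not both at six months, over all patients, alongside the coverage outcome. On that reading a late starter is correctly described. The authors considered timing, since the Discussion justifies six months by the minimum time a schedule needs. Follow-up is the same in both phases, and a common landmark is a recognised choice. The effect is small if most patients start soon after discharge. Finally, only a condensed article is shown, and date rules for a secondary outcome may sit in the full protocol or analysis plan.

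Much of this stands. The documents use the word incomplete, not failure, and nowhere say that the outcome is meant to measure drop-out between the two vaccines. A reader might infer either, but the text supports neither. The fixed six-month definition is sound for the primary coverage outcome.

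Two things do not fall away. The Discussion's rationale leaves enough time only for patients who start by about week 18, and nothing addresses later starters. Also, the article does not merely leave the definition to another document: it states one, without a condition on time since the first vaccine. A patient who is on schedule meets it.

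**Conclusion.** The concern holds as a minor point on one secondary outcome. By the documents' own interval, patients who start in about the last 8 weeks of follow-up (31% of the window) are labelled incomplete before the second vaccine is due. This applies to those still waiting for it; a patient given PPSV23 sooner would count as complete.

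The size in this trial cannot be computed. Under the stated assumptions the late share of starters runs from 0.2% to about 31%. At the planned completion rates, the spurious difference between phases runs from about 9 points in favour of the intervention to about 9 points against it, and is about 1 to 3 points under the earlier start times tried.

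A reader might infer that the rule favours the intervention, because its patients should start sooner. The documents do not establish that: they give no start times, and more starters in the intervention phase pushes the other way. Nor would a gap of about 15 points be a fair illustration. It requires 50% starters in both phases with uniform control starts (0.50 × 30.8% = 15.4%) and no late intervention starts. Completion would then be 34.6% and 50%, which does not match the planned 20% and 40%.

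**What to change.** Leave the primary outcome at six months and keep the total number of patients as the denominator. Split the patients with PCV13 only at six months into two groups, reported by phase:

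1. second vaccine due under the documents' own interval and not given, which becomes the incomplete rate;
2. second vaccine not yet due at six months.

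The two rates add up to the rate as now defined, so no information is lost.

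Time the split from the PCV13 administration date or, where that is absent, from the dispensing date in the national health data system (SNDS). The article describes checking administration but does not say that dates are recorded, so availability should be confirmed first.

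Treat any dispensing found after six months as descriptive only. SNDS lists what was delivered, not what was given. Section 2.4 also has the coordinating pharmacist inform GPs of the recommendation for unvaccinated patients at the end of follow-up, which may influence later dispensing.

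The Trial status section reports that follow-up has ended, so this is an analysis rule with no change to conduct. It costs one date rule, somewhat fewer events in the incomplete rate, and some approximation where only a dispensing date exists.

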### Intervention

2.4

During the control period, the patient management will be as usual: the pharmacist in the unit will do a medication reconciliation and check his pneumococcal vaccination status. If the patient is eligible for vaccination based on HCPH criteria [14] but not vaccinated according to three sources [20,21], the pharmacist will note it in the patient's medical record. During the month after discharge, the pharmacist of the unit will check pneumococcal vaccines prescription and notification of vaccination indication in the discharge letter by the department physician. Six months after the end of hospitalization, the coordinating pharmacist of the study will call the patient's usual community pharmacy to check vaccine dispensation. He will also call the patient's general practitioner and/or home care nurse to check the vaccine administration. Finally, the SNDS will be analyzed to check all vaccine dispensation.

Concerning the experimental stage, the pharmacist of the unit will also do medication reconciliation, check the vaccination status of patient and report it in the medical record. If it is negative, the pharmacist will communicate the vaccination benefit to the physician the vaccination benefit. Then the physician will suggest the pneumococcal vaccination and prescribe the protocol with patient agreement. He will note vaccination indication in the discharge letter for the GP. Before the patient returning home, the pharmacist will have a pharmaceutic discharge conversation with the patient and explain the benefits of vaccination and the protocol (dispensation and administration). The pharmacist will also send a pharmaceutic discharge letter to the patient's usual community pharmacy about pneumococcal vaccination. The follow-up procedure and the data collected will be the same for the two phases. For ethical reasons, the coordinating pharmacist will inform the GP of the recommendation to vaccinate all unvaccinated patients of the study at the end of their follow-up. The OPTIVACC study's flow of intervention is outlined in Fig. 2.

**Fig. 2 fig2:**
[figure not shown]
OPTIVACC study - flow of intervention.

### Blinding

2.5

This study is single-blind. Indeed, the patient will not know if he was included in control period or interventional period. However, due to intervention type and the study design, pharmacists and physicians of the participating units will know if the patient is included in observational or experimental stage because they must do or not the intervention.

### Sample size calculation

2.6

This study was designed according to a validated methodology of SW-CRT [23]. The Canadian meta-analysis from Taitel et al. suggests that the vaccine coverage risk ratio is 2,96 for intervention [19], but for this study, a less optimistic hypothesis was made.

Considering an intraclass correlation coefficient of 0.05, a power of 95 % and a two-sided alpha level of 5 %, a total of 684 patients must be included to highlight an absolute difference of 20 % between the control group (20 %) and the experimental group (40 %). Assuming 10 % of unusable data, the patient number were increased to 768, so 8 patients per unit and period.

### Data management

2.7

During this study, RedCap (REDCap 13.4.13 - © 2023 Vanderbilt University, Nashville, Tennessee, USA), a software allowing data collection, will be used. The software will allow access to the database to participants, according their role in the study. Furthermore, it saves any data change. Only authorized people will be able to get the access to electronic case report form (e-CRF), with a login and a password.

The software is hosted by a server of Nîmes University Hospital. All collected data will be saved every day on a secure network. Creation and settings of e-CRF, management during the study and data extraction will be done by the Department of Biostatistics, Epidemiology, Clinical Research and Health Economics.

### Statistical analysis

2.8

First, descriptive statistics of the population will be done. The quantitative variables will be reported as means and standard deviation or medians and quartiles, while qualitative variables will be expressed as headcounts and proportions.

Concerning the primary outcome, the variable to explain is a complete vaccination protocol. The vaccination rate after 6 months since discharge, between control and interventional, will be analyzed by mixed logistic regression model.

We consider a potential sensitivity analysis performed by age (≥65 years vs ≤ 65 years) and comorbidities (immunocompromised patients vs non-immunocompromised) by sequentially adjusting our statistical model for the potential confounders.

For the secondary outcomes, the matching between the SNDS data and declarations of drugstores about dispensations of vaccines will be access by calculating the kappa coefficient. The other outcomes with binary variable will be parsed by mixed logistic regression model. All statistical analysis above will be stratified by type of units (medicine or surgery) and type of health facility (university hospital or hospital).

Included patients headcount will be described and summarized in a flow chart.

The statistical analysis will be performed by the Department of Biostatistics, Epidemiology, Clinical Research and Health Economics of Nîmes University Hospital by using SAS Enterprise Guide V7.1 (SAS Institute, Cary, NC, USA) or R 3.5.1 (R Development Core Team (200918). R Foundation for Statistical Computing, Vienna, Austria) or a later version.

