**Methods:**

This study is a multicentric stepped-wedged randomized trial involving 12 units in 9 French hospitals (3 university and 6 local) during 4 periods of 90 days each. Three clusters will be made, each composed randomly of clinical and surgical units from one university hospital and clinical and surgical units of 2 local hospitals. For each period, one unit will have to include 16 non-vaccinated inpatients at risk of IPD. Patients in the control phase will receive usual care. During the interventional phase, the pharmacist will inform the physician on PV necessity, who will report recommendation and prescribe it at discharge. The pharmacist will perform a consultation and send a discharge letter to the patient's community pharmacist. The primary outcome will assess the impact of intervention on PV coverage after 6 months. Secondary outcomes will evaluate vaccines dispensing, uncompleted protocol rate and intervention process. A subgroup analysis between university and local hospitals and clinical and surgical units, respectively will be made.

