### Design

2.1

This study will be a multicentric prospective stepped wedge controlled randomized trial (SW-CRT) with 3 clusters and 4 periods. This design was chosen because it will not be possible to do an individual randomization of patients. Indeed, there would be a high risk of contamination bias as soon as the interventional strategy will take place in the unit with the medico-pharmaceutical collaboration: it will change the habits for all patients, including control patients. The cluster cross over will be in one direction only. A sequential permutation of each cluster from control to experimental period, determined by randomization, will be made after a set time of 90 days. All the clusters will start in the control phase and end up in the interventional phase. The study design is outlined in Fig. 1.

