### Settings/population

2.2

3 university hospitals and 6 local hospitals with clinical pharmacy activities in the region of Occitanie, France, have agreed to participate in this study. The 3 clusters will be made up of randomly selected hospitals and units. Each cluster comprises 4 units: 2 units (clinical and surgical) from the same university hospital and a clinical and surgical unit from different local hospitals. Hospital centers, units and number of patients to be included are described in Table 1. For this study, each unit will recruit 8 patients per period, so 64 patients during the period of inclusion. Therefore, a hospital will include 64 patients and a university hospital 128, totaling 768 patients for the entire study.

**Table 1 tbl1:** Hospital centers, units and number of patients to include.

Hospital center	Type of establishment	Unit	Unit type	Total number of patients to include
Nîmes	University hospital	General medicine	Clinical	64
		Digestive surgery	Surgical	64
Montpellier	University hospital	Internal medicine	Clinical	64
		Digestive surgery	Surgical	64
Toulouse	University hospital	Internal medicine	Clinical	64
		Vascular surgery	Surgical	64
Bagnols-sur-Cèze	Hospital	Gastroenterology	Clinical	64
Montauban	Hospital	Pneumology	Clinical	64
Saint-Gaudens	Hospital	General medicine	Clinical	64
Alès	Hospital	Surgery	Surgical	64
Perpignan	Hospital	Surgery	Surgical	64
Sète	Hospital	Surgery	Surgical	64

To qualify, patients must be over 18 years old and covered by the French National Health Insurance (NHI). They must be hospitalized in one of the units participating in this study and also need to be at risk of pneumococcal diseases and eligible to the pneumococcal vaccination according to the French high council of public health recommendations [14]. At admission, patients will receive medication reconciliation from the clinical pharmacist of the department. Patients requiring only a vaccine booster will not be included in the study. The vaccination status of the patient will be confirmed at least by 3 sources as recommended by French society of clinical pharmacy and high authority of health: patient or caregiver declaration, usual drugstore, patient's physician or medical records [20,21]. As last criteria, the patient will go back home at the end of hospitalization. The patient's consent will be obtained and recorded in the medical file, followed by regular monitoring visits carried out by a clinical research associate.

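### With three randomised clusters, an uncorrected mixed logistic regression rejects a true null about 8% of the time, not 5%, and the stated 95% power belongs to a different test

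*Protocol article*

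**What the plan says.** Section 2.1 describes a "stepped wedge controlled randomized trial (SW-CRT) with 3 clusters and 4 periods". Section 2.2 adds: "Each cluster comprises 4 units", so there are 12 units. In each cluster, two units belong to one university hospital and the other two to different local hospitals.

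Section 2.6 sizes the trial thus: "Considering an intraclass correlation coefficient of 0.05, a power of 95 % and a two-sided alpha level of 5" per cent. It requires 684 patients to detect 20% against 40%, raised to 768 for unusable data.

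Section 2.8 names the primary analysis: "The vaccination rate after 6 months since discharge, between control and interventional, will be analyzed by mixed logistic regression model". The binary secondary outcomes get the same type of model. The article does not give the level of the random effect, a period term, the test, or a small-sample method.

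**The concern.** The 5% and 95% in section 2.6 can only be read as properties of the analysis in section 2.8. A z-test with a known intraclass correlation and a fitted mixed model behave alike when there are many clusters. With three they do not. The between-cluster variance is then poorly estimated and often comes out at zero. In that case the model treats comparisons between clusters as almost free of cluster noise, and the standard error of the intervention effect is too small.

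Moving the random intercept to the 12 units does not reliably help. Units switch in groups of four, so any correlation shared within a group is missed.

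At stake are a false-positive rate above the stated level, confidence intervals that are too narrow, and a stated power that the analysis does not have.

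**Working it through.** **Inputs.** 3 clusters, 4 periods (section 2.1); 4 units per cluster (2.2); correlation 0.05, two-sided 5%, 20% against 40%, 684 patients (2.6). The abstract says "For each period, one unit will have to include 16 non-vaccinated inpatients at risk of IPD". Sections 2.2 and 2.6 say 8, but 8 × 12 × 4 = 384, whereas 16 × 12 × 4 = 768, so 16 matches the stated total.

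**Reproducing 684.** Hussey–Hughes variance with a random cluster intercept and fixed periods:

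Var = I·s²(s² + T·τ²) / [(I·U − W)s² + (U² + I·T·U − T·W − I·V)τ²]

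Here I = 3, T = 4, U = 3 + 2 + 1 = 6, W = 0 + 1 + 4 + 9 = 14 and V = 9 + 4 + 1 = 14. The bracketed coefficients are 18 − 14 = 4 and 36 + 72 − 56 − 42 = 10.

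With the control-arm variance 0.2 × 0.8 = 0.16 and 57 patients per cluster-period (684 / 12):
- s² = 0.16 × 0.95 / 57 = 0.002667 and τ² = 0.16 × 0.05 = 0.008
- Var = 3 × 0.002667 × 0.034667 / (0.010667 + 0.08) = 0.003059, so SE = 0.0553
- power = Φ(0.2 / 0.0553 − 1.96) = Φ(1.656) = 95.1%

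At 56 per cluster-period (672) it is 94.8%, so 684 is the smallest total reaching 95%. Then 684 / 0.9 = 760, and 760 / 48 = 15.8, rounded up to 16, gives 768. Other formulas tried do not return 684: averaged or pooled variance needs 864 or 912, and the Woertman design effect gives about 750–946.

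**Share due to the sizing variance.** At 684 the same formula gives 89.9% with the averaged variance (0.16 + 0.24) / 2 = 0.20, and 88.4% with the pooled 0.3 × 0.7 = 0.21. Much of the power gap therefore precedes any question about the model.

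**Simulated false-positive rate.** 20% in every cell, 14 to 16 patients per unit-period, period effects in the model, total random-intercept variance (0.05 / 0.95) × π²/3 = 0.173 on the logit scale, nominal two-sided 5%, Wald test against 1.96. Ranges cover separate runs of 1,500 to 12,000 replicates. At a true 8%, Monte Carlo error runs from about 0.7 points down to 0.25.

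| Fitted model | Correlation all between clusters | Split half and half | All between units |
|---|---|---|---|
| 3-cluster random intercept, SE allowing for the estimated variance | 7.4–8.1% | 8.0% | – |
| Same, SE holding the estimated variance as known | 8.5–10.2% | – | – |
| 12-unit random intercept | 12.5–14.5% | 8.1–9.5% | 5.5–5.8% |
| Cluster or unit as fixed effects | 4.2–5.6% | 4.2–4.7% | 4.3–4.7% |

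Placing the 0.05 on the proportion scale gives 7.4–7.5% for the first row, first column. The glmer routine in R gives 7.3–7.7%. A likelihood-ratio test gives 6.8%. Leaving period out, with no secular trend, gives 5.7–6.1%. The cluster variance was estimated as zero in about 16–28% of simulated trials.

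**Simulated power**, 20% against 40% (log odds ratio ln[(0.4/0.6) / (0.2/0.8)] = 0.98), about 672–684 patients: 84–92% with random intercepts and 83–88% with fixed effects. Part of the random-intercept power comes from its inflated error rate.

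**The case against.** The strongest reply is that section 2.8 writes down no Wald z-test, no level for the random effect and no reference distribution. A condensed article may leave these to a full protocol or analysis plan that is not shown. The result does depend on them: referring the 3-cluster fit to a t distribution with 6 degrees of freedom gives 2.8–3.0%, and unit intercepts are close to nominal if correlation lies only between units. This stands in part. The absence of such detail is not the finding, and nobody can say that the plan as written has a given error rate. What remains is that section 2.6 prints 5% and 95% from a known-variance test beside a named analysis that does not deliver them without correction. The t reference also overcorrects (below 0.1% with 2 degrees of freedom), so the remedy has to be chosen deliberately.

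A reader might infer a flat 10%, twice the nominal level. The documents do not support that: 10% appears with a 3-cluster intercept only when the standard error holds the variance as known. The 12–14% needs all correlation to sit at the randomised grouping. Two units per cluster share a hospital, but no effect common to all four is documented.

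A reader might also add drift in cluster rates between periods. At an assumed cluster autocorrelation of 0.9, 0.8 or 0.6 the random-intercept model exceeds 11%, but those values are not in the plan. With cluster fixed effects the rate is also above 5% there (7.7%, 9.0% and 12.8%). Drift is no part of this claim.

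Finally, three clusters allow only 3! = 6 orders, so a randomisation test cannot give p below 1/6. None is planned, so this is not an error; it only rules out that remedy.

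**Conclusion.** The point holds at moderate size. Without a small-sample correction, a 3-cluster random-intercept Wald test with period effects has a false-positive rate of about 8%, or up to about 10% under the less careful standard error. With unit intercepts it is about 6% to 14%, depending on where the correlation lies. The 95% power is not that of the named analysis, which simulates at about 84–92%; part of that shortfall comes from the control-arm variance used in sizing.

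This assumes a correlation of 0.05 that is constant over time, period effects in the model and no correction in the unseen plan. It is a calibration fault worth correcting. It does not invalidate the design. Confidence is medium, because the exact figure turns on choices that the article does not state.

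**What to change.** In section 2.8, make the primary model a logistic regression with phase, period and unit (12 levels), or the 3 clusters, as fixed effects. Report the mixed model as a sensitivity analysis, and do the same for the binary secondary outcomes. Comparisons by unit type and facility type remain possible, since phase-by-type interactions are still estimable. If the mixed model stays primary, state its random-effect level and period term, and use a small-sample method shown by simulation to hold 5% in this design.

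In section 2.6, replace 95% with the power of the chosen analysis: about 83–88% with fixed effects at 672–684 analysable patients. The Trial status section reports 646 included, so power at the achieved size will be lower than at 684.

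The change needs wording and one restated figure, and no new patients. The price is about 0 to 8 points of nominal power against the uncorrected mixed model. Fixed effects would reduce but not remove inflation if cluster rates drift. Since follow-up has ended, record whether the change was made before results by phase were seen; if not, report both models and say so.
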